	Critical Thinking	Halpern Critical Thinking Assessment^1^, Heuristic and Biases items^2^	2	Critical thinking will increase more for the MM group than for the SM group from t_1_ to t_4_ *(a* ^*1,2*^ *)* and this effect will be moderated by baseline endorsement of thinking dispositions *(b* ^*1,2*^ *)*	Mixed ANOVA, ANCOVA
	Thinking Dispositions	Actively Open-minded Thinking^1^, Need for Cognition^2^	3	Endorsement of critical thinking dispositions will increase more for the MM group than for the SM group from t_1_ to t_4_ *(a* ^*1,2*^ *)*	Mixed ANOVA
	Executive Control	Sternberg Working Memory Task	4	Executive control will increase more for the MM group than for the SM group from t_1_ to t_4_ *(a)* and this increase will mediate the relationship between levels of mindfulness and critical thinking performance following the intervention *(b)*	Mixed ANOVA, SEM
Secondary	Wellbeing	Warwick-Edinburgh Mental Wellbeing Scale	5	Wellbeing will increase and negative affect will decrease more for the MM group than for the SM group from t_1_ to t_4_	Mixed ANOVA
	Positive Affect and Negative Affect	Positive Affect and Negative Affect Schedule subscale	6	Positive affect will increase more for the MM group than for the SM group from t_1_ to t_4_ *(a)*	Mixed ANOVA
	Real-world Outcomes	Real-world Outcomes Inventory	7	Negative real-world outcomes will decrease more for the MM group than for SM group from t_1_ to t_4_	Mixed ANOVA
Manipulation Checks	Meditation Quality	Practice Quality-Meditation	8	Meditation quality will be positively associated with increases in mindfulness *(a)*, executive control *(b)* and critical thinking *(c* ^*1,2*^ *)* and meditation quantity *(d)*, task enjoyment *(e)* and task difficulty *(f)* and it will be higher in the MM group and across time.	Correlation, Mixed ANOVA
	Meditation Quantity	Total Minutes Spent Meditating	9	Meditation quantity will be positively associated with increases in mindfulness *(a)*, executive control *(b)* and critical thinking *(c* ^*1,2*^ *)* and meditation quality *(d)*, task enjoyment *(e)* and task difficulty *(f)* and will not differ across time or groups.	Correlation, Mixed ANOVA

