### Sample size (Incl. flow chart)

The statistical program G*Power was used to conduct power analysis in order to determine the appropriate sample size. Adhering to Cohen’s [48] guidelines for small (*r* = 0.1), medium (*r* = 0.3), and large (*r* = 0.5) effects, two-tailed alpha of .05 was assumed for all tests. With 2 groups, 6 measurements, an assumed correlation among repeated measures of 0.3 (typically low in such research; [49]) as well as a medium effect size (again typical in research on the cognitive effects of mindfulness; [10]) and a power of 0.8, the recommended sample size for mixed (repeated-measures and between factors) ANOVA was 56. As it is recommended that the sample size be a multiple of the number of measurements, a sample of at least 60 will be sought, 30 per group. Because of an anticipated attrition rate of 20 %, 38 participants are required per group i.e. 78 in total. Previous studies using Headspace have reported attrition rates between 20 and 40 % [41, 44]. We expect an attrition rate closer to 20 % because of the incentives in the form of course credit, lunches provided at data collection and free subscription to Headspace for 6 months following the intervention.

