### Statistical analysis

Data will be primarily analysed through a series of 2 × 2 (time – pre, post x group – mindfulness meditation, sham meditation) mixed ANOVAs for each outcome measure using SPSS. The time x group interaction affects will be assessed in order to investigate differences in between the experimental group and the control group in the amount of change on the dependent variables. Correlations between manipulation check measures will also be examined as will their correlations with FFMQ change scores. AMOS will allow simple mediation analyses to be conducted using Structural Equation Modelling (SEM) to test whether executive function, meditation quality and adherence are mediators of any potential relationship between mindfulness and critical thinking. As noted above, these tests will be adequately powered – including SEM analyses (see [69], for evidence of adequate power for simple mediation using SEM in samples as small as *n* = 30). Our analyses will take an intention-to-treat approach and missing data will be treated with a baseline-observation-carried-forward approach. See Table 1 for specific hypotheses.

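### The mediation analyses are called adequately powered with no calculation behind the claim, and their exposure is an undated mindfulness score instead of the randomised arm

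*Protocol article*

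**What the plan says.** The Statistical analysis section plans simple mediation models in AMOS "to test whether executive function, meditation quality and adherence are mediators of any potential relationship between mindfulness and critical thinking". It says that these tests, SEM included, will be adequately powered. It refers back to what was noted earlier and cites a source "for evidence of adequate power for simple mediation using SEM in samples as small as" n = 30.

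The only earlier power statement is under Sample size. There "two-tailed alpha of .05 was assumed for all tests", medium is defined as r = 0.3, and the inputs are given as "With 2 groups, 6 measurements, an assumed correlation among repeated measures of 0.3" "as well as a medium effect size". The result is "a power of 0.8, the recommended sample size for mixed (repeated-measures and between factors) ANOVA was 56". The target is then at least 60, with 38 per group (78 in total as written) to allow for 20% attrition.

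In Table 1, under the primary outcomes, hypothesis 4b expects that executive control will rise and that "this increase will mediate the relationship between levels of mindfulness and critical thinking performance following the intervention". Hypothesis 9 expects that meditation quantity "will not differ across time or groups". Hypothesis 8 expects meditation quality to be higher in the mindfulness arm.

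**The concern.** The central question under The current study is causal: does regular practice help critical thinking by improving executive function? Two features of the planned analysis weaken any answer.

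First, the assurance of adequate power has nothing behind it in the article. A null indirect effect could then be taken as fair evidence against mediation when the test had little chance of finding a medium effect.

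Second, the model starts from a questionnaire score and not from the randomised arm. Associations between a mindfulness score, executive function and critical thinking are open to confounding whatever the allocation. Two of the three named mediators also fit poorly in the sequence, depending on how the undated exposure is read.

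**Working it through.** **1. What the stated calculation covers.** Inputs from Sample size: 2 groups, m = 6 measurements, correlation 0.3, two-sided alpha 0.05, power 0.8. Assumption: medium was entered as f = 0.25, since the f used is not stated. For the between-groups test of a repeated-measures ANOVA,

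λ = f²·N·m / (1 + (m − 1)·ρ) = 0.0625 × 56 × 6 / (1 + 5 × 0.3) = 21 / 2.5 = 8.4.

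The noncentral F with 1 and 54 degrees of freedom then gives power 0.812, so N = 56 is reproduced. The calculation contains no indirect effect and no path from mediator to outcome, so it says nothing about SEM power.

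**2. Power for one path at r = 0.3.** Power ≈ Φ(atanh(r)·√(n − 3) − 1.96), with atanh(0.3) = 0.3095:
- n = 60: Φ(0.3095 × 7.550 − 1.96) = Φ(0.377) = 65%
- n = 78: Φ(0.3095 × 8.660 − 1.96) = Φ(0.720) = 76%

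A joint-significance test needs both paths significant, so it cannot exceed the power of either path. Squaring gives a rough check: 0.647² = 42% at n = 60 and 0.764² = 58% at n = 78. The simulated values are slightly lower because path b is estimated with the exposure also in the model.

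**3. Power for the indirect effect.** Model: M = aX + error and Y = bM + c′X + error, all standardised, with a = b = 0.3 (an assumption, because the protocol gives no paths), c′ = 0 and two-sided alpha 0.05. Joint and Sobel tests: 20,000 replicates. Bootstraps: 1,500 replicates of 1,000 resamples.

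| n | Joint | Percentile bootstrap | Bias-corrected bootstrap | Sobel |
|---|---|---|---|---|
| 30 | 11.8% | 12.2% | 19.7% | 4.1% |
| 60 | 39.3% | 39.1% | 51.0% | 20.3% |
| 78 | 55.6% | 55.3% | 65.3% | 34.9% |

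Two groups of 38 make 76, not 78. At 76 the joint test gives 54.0%. A direct effect of c′ = 0.3 raises the joint test by about 5 points (44.3% at 60, 60.6% at 78). Power of 80% needs about 116 participants (joint) or about 144 (Sobel). At n = 30, two paths of 0.5 give 57% by the joint test, and two of 0.59 give 78%.

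**4. Exposure and order.** Data collection places the mindfulness questionnaire, the Sternberg task and the critical thinking measures at baseline (T1) and after the intervention (T4) only. Quality is collected in weeks 2 and 4. Minutes accrue between T1 and T4 (Adherence). Statistical analysis gives no time point for the mindfulness variable, so each reading has to be tried:

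| Exposure | Executive function (T4) | Quality (weeks 2 and 4) | Adherence (T1 to T4) |
|---|---|---|---|
| T4 mindfulness score (most natural for 4b) | same visit, order untestable | precedes exposure, cannot mediate | precedes exposure, cannot mediate |
| T1 mindfulness score (fits 4b poorly) | order possible | order possible | order possible |
| Randomised arm | order possible | order possible, consistent with hypothesis 8 | conflicts with hypothesis 9: no arm difference expected |

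Under either score reading, randomisation does not protect the paths that start from mindfulness.

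**5. Power for the arm-based model.** Arm → T4 executive function → T4 critical thinking, adjusted for both T1 scores. Assumptions: arm effect d = 0.5 to 0.63, b = 0.3, T1–T4 correlation 0.3 to 0.6. The upper d is r = 0.3 converted at 1:1 allocation: 2 × 0.3 / √(1 − 0.09) = 0.63. The joint test gives roughly 30 to 55% at n = 60 and 45 to 70% at n = 78. The low ends belong to d = 0.5 with correlation 0.3, and the high ends to d = 0.63 with correlation 0.6.

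**The case against.** The main comparisons are the 2 × 2 mixed ANOVAs by arm, and nothing here touches them. That stands.

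The protocol's medium effect was set for an ANOVA, not for mediation paths, and the answer depends on the test and on the number analysed. That also stands. A reader might quote a single figure just under 40% as the power of this analysis, but the documents do not support that. It is conditional on 60 analysed, both paths at 0.3, no direct effect and a joint or percentile-bootstrap test. Intention-to-treat with baseline carried forward could put up to 76 to 78 records in the model, though carried-forward records add little real information. Paths near 0.5 would give high power at n = 60 (94% by the joint test).

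A reader might also infer that the cited n = 30 source is wrong. It is not available here and is not judged. The point is only that the article gives no path sizes under which n = 30 would be enough.

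Finally, a reader might infer that the exposure is definitely the post-intervention score, that the order is impossible for every mediator, and that quality should go along with adherence. The text does not bear this out. The time point is inferred from hypothesis 4b, where the closing phrase may qualify critical thinking alone. Executive function on that reading is of untestable order, not impossible order. With arm as exposure, quality is correctly ordered and agrees with hypothesis 8.

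**Conclusion.** The concern holds in a limited form. The claim that the SEM analyses are adequately powered has no calculation behind it in the article, and it fails at the protocol's own medium r = 0.3 applied to both paths: about 12% at n = 30, 39% at n = 60 and 56% at n = 78 (joint test). With no direct effect, the range across tests at n = 60 to 78 is about 20 to 65%. No variant tried, with or without a direct effect of 0.3, reaches 80%. These figures rest on assumed path sizes.

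The exposure is a mindfulness score of unstated date, so the mediation model does not use the randomised contrast that the causal question calls for. Adherence as a mediator fails if the exposure is the post-intervention score or the arm. Quality fails only on the first of these. The defect concerns the mediation analyses alone and should be corrected before they are run.

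**What to change.** - In Statistical analysis and hypothesis 4b, define the exposure as randomised arm and fit arm → T4 executive function → T4 critical thinking, adjusted for T1 executive function and T1 critical thinking. Report the indirect effect with a bootstrap confidence interval.
- Label the analysis exploratory. Even in this model the path from executive function to critical thinking is non-randomised and measured at one visit, and baseline adjustment only reduces that problem.
- Do not test adherence as a mediator. Analyse it as a within-arm dose-response relationship.
- Keep meditation quality only as a mediator of arm.
- Delete the adequate-power and n = 30 statement for SEM. Replace it with a conditional range for the model actually used. For arm with T1 covariates this is roughly 30 to 55% at n = 60 and 45 to 70% at n = 78, with the assumptions printed beside it (d = 0.5 to 0.63, b = 0.3, T1–T4 correlation 0.3 to 0.6). The figures for a continuous exposure should not be carried over to that model.

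The cost is a change of analysis wording with no new data, and a less favourable power statement.

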## Methods/design

### Design

The CONSORT guidelines for evaluation of randomised controlled trials [45], the CONSORT extension for non-pharmacological treatment interventions [46], the SPIRIT checklist of protocol items and the TIDIER checklist for intervention description and replication [47] were adhered to in the design of this study and this protocol paper.

This study involves a two-arm randomised-controlled superiority trial with one intervention condition, guided mindfulness meditation, and one active-control condition, sham meditation. The design employed is a 2 (condition) X 2 (time) parallel-group design which is explanatory in nature. Measurement will take place at baseline (i.e. before randomisation, T1) and 6 weeks after baseline (T4). The delivery of the content of both the intervention condition and the active-control condition will take place between T1 and T4. Manipulation checks will be carried out to assess intervention acceptability, technology acceptance and meditation quality 2 weeks after baseline (T2) and 4 weeks after baseline (T3). See Table 2 for a description of the procedure.

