### Data collection

Primary and secondary measures will be taken at baseline and following the end of the intervention (see Table 2). In terms of primary outcome measures, we will assess critical thinking using the Halpern Critical Thinking Assessment [51] and items from the Heuristics and Biases literature [5], mindfulness with the Five Factor Mindfulness Questionnaire (FFMQ;[52]), thinking dispositions with the Need for Cognition scale [53] and the Actively Open Minded thinking scale [8] and executive function with the Sternberg working memory task [54] presented on Inquisit software [55]. Objective measures of meditation adherence (no. of sessions initiated and completed and no. of minutes spent meditating) will be gathered through the Headspace app. Secondary measures will assess effects on wellbeing in order to compare with previous studies employing Headspace. The Positive Affect and Negative Affect Schedule [56] and the Warwick-Edinburgh Mental Wellbeing Scale [57] will be used. All of the measures except the Sternberg Working Memory Task will be presented using SurveyGizmo. Data Collection will take place during the week preceding the start of the intervention in the PC Suites of the School of Psychology at NUI Galway. Three sessions will be scheduled in order to facilitate attendance at different times, each of which will be able to accommodate up to 30 participants comfortably. A break with food and refreshments will be given half way through the procedure. This data collection approach will be repeated during the week following the end of the intervention.

Manipulation checks will be carried out during weeks 2 and 4 of the intervention and will focus on mindfulness meditation quality and task expectations, enjoyment and difficulty. Mindfulness meditation quality will be assessed using the 6 item Practice Quality- Mindfulness questionnaire [58] while task expectations, enjoyment and difficulty will be assessed using the Technology Acceptance Questionnaire [59] and Intervention Acceptability items [60]. These questionnaires will be administered online using SurveyGizmo through a link which will be distributed by email.

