There are however some weaknesses associated with this study also. While every effort was made to ensure that the only difference between the guided mindfulness meditations and the guided sham meditations would be the provision of specific instructions to do with building specific mindfulness skills in the experimental condition, it could be that this manipulation makes these guided sessions more engaging and enjoyable than the guided sham meditations. This could lead to differences in attrition rates across the two conditions. Attrition rates in general could be larger than expected which may affect the statistical power of the analyses. Finally, participants will be drawn from the student population only and so any conclusions made based on this study may not be generalizable to the wider population. However, critical thinking is a skill which is of particular importance as an outcome of university education and therefore this study may have practical benefits.

Many companies, universities and other institutions are introducing mindfulness programmes with the promise of improving thinking skills [72]. While there are theoretical and historical reasons supporting this view, it has not been adequately investigated. The significance of this study lies in its rigorous approach to investigating this claim for the first time in the context of an RCT.

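### Baseline-observation-carried-forward as the only missing-data rule scores every dropout as unchanged: it shrinks the arm difference, is not reliably conservative, and biases the minutes–gain correlations

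*Protocol article*

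**What the plan says.** The Statistical analysis section plans a 2 × 2 mixed ANOVA for each outcome: "The time x group interaction affects will be assessed in order to investigate differences in between the experimental group and the control group". The same paragraph adds correlations of the manipulation checks with change in the mindfulness questionnaire, and mediation models in AMOS. It then adopts intention-to-treat and says that "missing data will be treated with a baseline-observation-carried-forward approach". No other missing-data method is named, its scope is not limited to the ANOVAs, and no reason is given for assuming that dropouts do not change.

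The Design section puts outcome measurement at T1 and T4 only. The sample size section plans for 20% attrition, while noting: "Previous studies using Headspace have reported attrition rates between 20 and 40" per cent. The Discussion considers that the mindfulness sessions might be more engaging than the sham ones and adds: "This could lead to differences in attrition rates across the two conditions". Table 1, hypothesis 13, predicts no difference in attrition between groups and a negative association of attrition with minutes meditated. Hypothesis 9 reads in part: "Meditation quantity will be positively associated with increases in mindfulness"; executive control and critical thinking follow in the same row. Minutes come from the app accounts (Adherence section), so they can exist for people with no T4 data.

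**The concern.** With a single follow-up, carrying the baseline forward amounts to asserting that each dropout changed by nothing on every outcome. Three results follow.

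- The arm difference shrinks when dropouts would have responded as completers do.
- When both arms improve, for instance because the same tests are taken twice, the arm with more dropouts receives more zeros. Unequal dropout then becomes an apparent treatment difference.
- Dropouts combine few app minutes with an imputed zero gain, so a positive association between minutes and gain can appear where none exists, in the direction the trial predicts.

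At stake are the size of every pre–post arm comparison and the credibility of the dose–response findings.

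**Working it through.** **Inputs from the article.** Two-sided alpha 0.05 and correlation between measurements ρ = 0.3 (sample size section). Attrition 20% planned, 20–40% in earlier app studies. Enrolment: 30 / 0.80 = 37.5, rounded up to 38 per group as the article states. Twice 38 is 76, but the article gives 78 in total, so I use 39 per arm.

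**Assumptions not in the article.** True effect δ = 0.50 SD. Gain shared by both arms μ = 0 to 0.8 SD. App minutes averaging 200 (SD 60) in completers and 75 (SD 50) in dropouts, truncated to 0–300 (30 sessions of ten minutes).

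**Formulas.** The time × group test is a t-test on change scores. With dropout p1 (mindfulness) and p0 (sham):

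- expected estimate = (1 − p1)(μ + δ) − (1 − p0)μ
- variance of change in an arm = (1 − p) × 2(1 − ρ) + p(1 − p) × (mean change of completers)²

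**1. Equal dropout.** The estimate reduces to (1 − p)δ. At 20%: 0.80 × 0.50 = 0.40 SD. At 40%: 0.60 × 0.50 = 0.30 SD.

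**2. Power at 20% dropout, δ = 0.50.**

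- Carried forward, μ = 0: variances 0.8 × 1.4 + 0.16 × 0.25 = 1.16 and 0.8 × 1.4 = 1.12; SE = √(2.28/39) = 0.242; 0.40/0.242 = 1.65; power 37% (35% if μ = 0.5).
- Completer change scores: 39 × 0.8 = 31.2 per arm; SE = √(1.4 × 2/31.2) = 0.300; 0.50/0.300 = 1.67; power 38%.
- Completers with baseline as covariate: SE = √((1 − 0.09) × 2/31.2) = 0.242; 0.50/0.242 = 2.07; power 53%.

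At 40% dropout the same three are 29% (26% if μ = 0.5), 29% and 42%. The gap between 37% and 53% is therefore almost entirely due to baseline adjustment.

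**3. Unequal dropout, 20% mindfulness and 40% sham, no true effect.** The estimate is (0.40 − 0.20)μ.

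| μ | False difference | SE (ρ = 0.3) | Type I error |
|---|---|---|---|
| 0 | 0 | – | 5% |
| 0.4 | 0.08 | √((1.146 + 0.878)/39) = 0.228 | 6.4% |
| 0.8 | 0.16 | √((1.222 + 0.994)/39) = 0.238 | 10.2% |

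Simulations of these scenarios range from 6% to 11%. With ρ = 0.7 instead of the article's 0.3, the last two rows become 8% and 16%. With a smaller gap (20% and 30%) and μ = 0.4, the false difference is 0.04 SD and the error rate 5.3%.

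With δ = 0.50 and μ = 0.4, the same 20%/40% pattern gives 0.8 × 0.9 − 0.6 × 0.4 = 0.48. The reverse pattern gives 0.6 × 0.9 − 0.8 × 0.4 = 0.22.

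**4. Minutes against gain, true association zero, N = 78, ρ = 0.3.** The covariance created is p(1 − p) × (difference in mean minutes) × μ. At 20% dropout and μ = 0.4 it is 0.16 × 125 × 0.4 = 8. Ignoring truncation, the SD of minutes is √(0.8 × 3600 + 0.2 × 2500 + 0.16 × 125²) = 76.7, and the SD of imputed gain is √1.146 = 1.07. Hence r = 8/(76.7 × 1.07) = 0.10. Simulation gives the same r and about 10% false positives, nearly all of them positive. At 40% dropout, r is about 0.16 and the rate is 26–31%, depending on the minutes assumed. For gains of 0.3 to 0.5 SD the rates are about 6–16% at 20% dropout and 16–41% at 40%. With zero mean gain, r is zero and there is no excess.

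**The case against.** **It depends on the estimand.** If people who leave also stop practising and lose any arm difference, the intention-to-treat effect at equal 20% dropout is itself 0.80 × 0.50 = 0.40. Carried-forward data then give the right answer, and a missing-at-random analysis (0.50) gives too much. This stands as a limit: the rule cannot be called biased under every assumption. It does not justify the rule, because the article offers no reason to think that dropouts stay at or return to baseline.

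**The rule is conservative.** A reader might equally infer that it always works against mindfulness. Neither inference is general. The Discussion's worry implies fewer dropouts under mindfulness. In that direction a shared gain pushes the estimate up: a null effect looks positive, while a true 0.50 comes out at 0.48, almost unbiased. The 0.22 result needs the opposite pattern and should not be taken as the expected case.

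**The attrition rates are too pessimistic.** Largely right. The plan is 20%, with incentives given as the reason; 40% is only the top of earlier experience. The Discussion says that attrition could differ, while hypothesis 13 predicts that it will not.

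**Power.** A reader might infer that the rule costs much power or wastes the enlarged sample. It does not. The inflation is meant to leave about 60 completers, and 78 × 0.80 = 62.4 does so. Only the imputed rows add no information.

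**Scope.** The rule may be meant for the arm comparison alone, and the correlations are manipulation-check hypotheses rather than the main comparison. The article does not restrict the rule, so the point needs to be settled in the text. That the checks in weeks 2 and 4 have no baseline to carry forward is a detail an article may leave out, and I do not press it.

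**Conclusion.** The concern holds in moderate form and should be fixed. It rests on a rule that the article states, not on something left to a later plan.

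- **Shrinkage** to 0.80 of the effect at the planned attrition is exact algebra, given equal dropout and dropouts who would have responded like completers.
- **A false difference** needs both unequal dropout and a non-zero shared gain. The documents give no figure for that gain, and the type I inflation is modest at the article's own correlation.
- **The correlation artefact** needs a non-zero mean gain and lower minutes among dropouts. Hypothesis 13 predicts the second. It is the larger distortion, though in a secondary set of hypotheses.

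The documents do not support a claim that the trial's headline result is bound to be wrong, or that the rule materially reduces power.

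**What to change.** Replace the rule in the Statistical analysis section.

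- **Primary arm comparison:** a likelihood-based mixed model including all randomised participants, or ANCOVA adjusted for baseline with multiple imputation. The imputation model should include arm, baseline, app minutes and whatever T2 and T3 checks are available.
- **Mediation:** full-information maximum likelihood.
- **Correlations:** observed changes only. Carried-forward values should not enter the correlations or the mediation models.
- **Sensitivity:** keep baseline-observation-carried-forward as one sensitivity analysis of the arm comparison, beside an analysis over a range of departures from missing-at-random. One carried-forward run is a single scenario and does not probe that assumption by itself.

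The cost is revised wording and a little more analysis; no new data are needed. The replacement relies on missing-at-random, which one follow-up cannot verify, and T2 and T3 checks may be absent for early dropouts. Baseline adjustment also raises power, but that gain should not be credited to dropping the carried-forward rule.
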